## Abstract

**BACKGROUND AND OBJECTIVES::**

There has been renewed interest in the use of external lumbar drainage (ELD) of cerebrospinal fluid (CSF) to reduce intracranial pressure after traumatic brain injury (TBI). Although the evidence is retrospective and thus confounded by selection bias, it is critical that a phase 1 trial systematically identify “select” patients who would gain benefit of intracranial pressure (ICP) reduction from lumbar drainage. The aim of this study is to evaluate safety and feasibility of controlled CSF ELD in reducing ICP burden and improving outcomes of select severe TBI patients.

**METHODS::**

The study will include 30 severe TBI patients with a Glasgow Coma Scale score ≤9 who will be randomized to usual treatment, usual treatment plus early ELD placement if initial ICP ≤20 mm Hg, or late ELD if ICP ≥20 mm Hg as first intervention in tier 2 of Seattle International Brain Injury Consensus Consortium protocol.

**EXPECTED OUTCOMES::**

It is expected that the incidence of severe neurological worsening events as per Seattle International Brain Injury Consensus Consortium will not be different between the control and intervention groups.

**DISCUSSION::**

A multitude of clinical trials to advance or discover new treatments of severe TBI have remained unfruitful. Recent understanding of the glymphatic system in the brain is suggestive that extraventricular CSF drainage may be very useful in reducing ICP. The natural avenue for this is through ELD. To avoid past mistakes by jumping into an advanced stage trial, we intend to conduct a phase 1 safety and feasibility trial to identify ‘select’ patients in whom ELD may be performed safely and may serve as a significant change of therapeutic approach to such patients with traumatic intracranial hypertension.

ABBREVIATIONS:cIRBcentralized Institutional Review BoardDSMBData and Safety Monitoring BoardELDexternal lumbar drainageKUMCKansas University Medical CenterLARlegally authorized representativeMTBIMilitary Traumatic Brain Injury InitiativeNPINeurological Pupillary indexSAEsserious adverse eventsTBItraumatic brain injury.

## BACKGROUND AND RATIONALE

Management of moderate-severe traumatic brain injury (TBI) consists of early screening, diagnosis, resuscitation, and surgery (if indicated), followed by specialized neurological intensive care to treat raised intracranial pressure (ICP).^1-3^ Beyond surgery, the cornerstone of TBI treatment pertains to management of elevated ICP which has been associated with improved outcomes by mitigating secondary injury.^4-10^ However, in the past 2 decades, few trials have evolved the management of severe TBI, most failing in phase 3.^11-14^

In an “Opinion” published in JAMA, titled *“Will We Ever Make Headway in Severe Traumatic Brain Injury Treatment Trials?*,*”* the authors emphasize that *“the selection of the right patients for the right therapy is essential if studies are to identify effective treatments.”*^15^ Such a paradigm change may involve *“improving an existing, proven and effective therapeutic intervention in the management of severe TBI and make it more effective.”* One such intervention is cerebrospinal fluid (CSF) drainage to lower ICP.

We previously conducted a systematic review of lumbar CSF drainage in patients with severe TBI that included 9 articles from 6 studies with a total of 110 patients.^16^ Nearly all studies included patients in whom external lumbar drainage (ELD) was performed if raised ICP was refractory to medical therapy. The ICP reduction occurred immediately, and the pooled effect size was −19.5 mm Hg (95% CI: −17.9 to −21.0 mm Hg). Only 1 patient with a previous operated temporal hemorrhage suffered uncal herniation requiring craniectomy but thereafter had a good outcome. Subsequently, more studies have been published demonstrating no increase in the risk of downward cerebral herniation.^17-20^ Indeed, Stevens et al^20^ demonstrated tonsillar elevation rather than descent from ELD, likely due to reduction of supratentorial ICP.

However, we must be vigilant of the selection bias of patients in these retrospective studies. Therefore, we designed a phase 1 safety and feasibility study of early ELD to abort traumatic intracranial hypertension.

## STUDY GOALS AND OBJECTIVES

The objective of this study is to evaluate safety and feasibility of controlled CSF ELD in reducing ICP burden and improving outcomes of select severe TBI patients.

### Specific Aims

#### Primary Aims

To determine whether controlled CSF external lumbar drainage to reduce ICP burden after severe TBI in select patientsis associated with an increase incidence of neuroworsening events (*Safety*)can be successfully performed when indicated (*Feasibility*)

#### Secondary Aims

To determine whether routine quantitative pupillometry can be used for safety determination for ELD by evaluating:Correlation of automated pupillometry-derived Neurological Pupillary Index (NPI) with ELD safety scoreIf NPI is temporally reduced before occurrence of any “critical neuroworsening event”

## STUDY DESIGN

The aim of this study is to determine the safety and feasibility of ELD to reduce ICP in select severe TBI patients in a phase 1 clinical trial in a multisite randomized, allocation-concealed, open-label, safety and feasibility clinical trial. The study protocol is written in accordance with the ‘Standard Protocol Items: Recommendation for Interventional Trials’ guidelines.

### Human Subjects

#### Inclusion Criteria

18 to 65 years of ageGlasgow Coma Scale (GCS) score 3 to 8ICP monitor in placePupils symmetric and bilaterally reactiveMidline shift ≤ 5 mm at the level of foramen of Monro on admission or postoperative brain CTPatent (complete or partial) quadrigeminal cisterns on admission or postoperative brain CTEnrollment up to 48 hours after injury (rescreening of patients can be performed if surgery changes exclusion criteria). First randomization and intervention can be commenced within 48 hours of injuryELD safety score ≥5

#### Exclusion Criteria

Cisterns on CT completely effacedGCS 3 with dilated and fixed pupilsUncal or tonsillar herniation on admission or postoperative brain CTTemporal lobe contusions with effaced ipsilateral cisternPenetrating TBIPrimary decompressive craniectomyPregnancyPrisonersPatients previously lacking capacity to consent or refuse treatment, or with advanced directives to forego aggressive carePreexisting conditions affecting functional status or life expectancy to less than 1 yearContraindications for ELD placement: uncorrected coagulopathy, unreversed use of anticoagulants or antithrombotics, thrombocytopenia <50 000, uncorrected international normalized ratio (INR) > 1.4, or severe spinal deformity.Posterior fossa hemorrhage

## METHODOLOGY

### Usual Treatment

All patients will receive usual treatment as per evidence-based guidelines and Seattle International Brain Injury Consensus Consortium (SIBICC) algorithm (Table 1).^21,22^ Either ventricular or parenchymal ICP monitors may be used. Hourly neuromonitoring will be performed including automated infrared pupillometry, GCS score, ICP, and motor examination. The NPI is an ordinal index ranging from 0 to 5, with a value of less than 3, considered abnormal pupillary reactivity based on prospective studies.^23,24^

**TABLE 1. T1:** SIBICC Treatment Algorithm

Tier 0
Admission to ICU
Endotracheal intubation and mechanical ventilation
Serial evaluations of neurological status and pupillary reactivity
Elevate HOB 30°-45°
Analgesia to manage signs of pain (not ICP directed)
Sedation to prevent agitation, ventilator asynchrony, etc. (not ICP directed)
Temperature management to prevent fever
Measure core temperature
Treat core temperature above 38°C
Consider antiseizure medications for 1 wk only (in the absence of an indication to continue)
Maintain CPP initially ≥60 mm Hg
Maintain Hb >7 g/dL
Avoid hyponatremia
Optimize venous return from head (eg, head midline, ensure cervical collars are not too tight)
Arterial line for continuous blood pressure monitoring
Maintain SpO_2_ ≥94%
Recommended interventions
Insertion of a central line
End-tidal CO_2_ monitoring
Tier 1
Maintain CPP 60-70 mm Hg
Increase analgesia to lower ICP
Increase sedation to lower ICP
Maintain PaCO_2_ at low end of normal (35-38 mm Hg/4.7-5.1 kPa)
Mannitol by intermittent bolus (0.25-1.0 g/kg)
Hypertonic saline by intermittent bolus
CSF drainage if EVD in situ
Consider placement of EVD to drain CSF if parenchymal probe used initially
Consider antiseizure prophylaxis for 1 wk only (unless indication to continue)
Consider EEG monitoring
Tier 2
Mild hypocapnia range 32-35 mm Hg/4.3-4.6 kPa
Neuromuscular paralysis in adequately sedated patients if efficacious
Perform MAP Challenge to assess cerebral autoregulation and guide MAP and CPP goals in individual patients
Should be performed under direct supervision of a physician who can assess response and ensure safety
No other therapeutic adjustments (ie sedation) should be performed during the MAP Challenge
Initiate or titrate a vasopressor or inotrope to increase MAP by 10 mm Hg for not more than 20 minutes
Monitor and record key parameters (MAP, CPP, ICP, and PbtO_2_) before during and after the challenge
Adjust vasopressor/inotrope dose based on study findings
Raise CPP with fluid boluses, vasopressors and/or inotropes to lower ICP when autoregulation is intact
Tier 3
Pentobarbital or thiopentone coma titrated to ICP control if efficacious
Secondary decompressive craniectomy
Mild hypothermia (35-36°C) using active cooling measures

CPP, cerebral perfusion pressure; CSF, cerebrospinal fluid; HOB, head of bed; ICP, intracranial pressure; ICU, intensive care unit; MAP, mean arterial pressure; PbtO2, partial pressure of brain oxygen.

### Intervention

ELD placement will be performed bedside or in operating room if patient is undergoing surgery but not under radiographic guidance and connected to the LimiTorr™ drainage system (Integra Neurosciences), and zero-leveled at the level of the tragus. The LimiTorr™ provides volume-limited drainage and shuts off at a maximum drainage of 10 mL/hour, by always leaving 10 mL of fluid in the 20 mL shut-off-burotrol. The burotrol will be primed with 10 mL of sterile water or saline and will only be drained to a maximum mark of 10 mL on the burotrol—stickers will be placed on the burotrol to ensure adherence to protocol. However, should overdrainage occur in a rare instance, the ELD will be clamped for 1 hour.

### Randomization

The study will enroll 30 severe TBI patients who will undergo 2-stage randomization into usual treatment, usual treatment plus early ELD placement if ICP ≤ 20 mm Hg, or late ELD if ICP ≥ 20 mm Hg (Figure). The process of randomization will be centralized through a secure computerized site.

**FIGURE. F1:**
[figure not shown]
Randomization process. ELD, external lumbar drainage; GCS, Glasgow Coma Scale; ICP, intracranial pressure; SIBICC, Seattle International Severe Traumatic Brain Injury Consensus Conference; TBI, traumatic brain injury.

### Outcomes

#### Primary Outcomes

Feasibility: We will calculate proportion of patients who are randomized to each intervention and receive it.Safety: Frequency of critical neuroworsening adverse events between the intervention and treatment arms as adjudicated by Data and Safety Monitoring Board (DSMB).

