## SAFETY CONSIDERATIONS

### Risks to Human Subjects

Critical neuroworsening events related to ELD and CSF drainage are neurological worsening events such as decrease in GCS score, development of new motor deficit, or a cerebral herniation event, and rarely death (Table 2). Given the greatest risk of neuroworsening from herniation is soon after drainage is commenced, all patients will have neurological checks ie GCS score, ICP measurement, automated pupillometry for pupillary size, symmetry and NPI performed every 15 minutes for 1 hour after ELD placement, and start of CSF drainage. If NPI drops <3 within the first hour, a head CT may be obtained to review any craniocaudal shift. After the first hour, measurements will be performed hourly.

**TABLE 2. T2:** Neuroworsening Events

Critical neuroworsening events per SIBICC protocol
1. Spontaneous decrease in the GCS motor score of ≥1 points (compared to previous exam)
2. New decrease in pupillary activity
3. New pupillary asymmetry or bilateral mydriasis
4. New focal motor deficit
5. Herniation syndrome or Cushing Triad which requires an immediate physician response

GCS, Glasgow Coma Scale.

Based on inclusion/exclusion criteria, we analyzed the severe TBI BTF-New York State TBI-trac database from 1997 to 2007, with 1100 patients. The inclusion criteria applied to 47% of all severe TBI patients admitted over 10 years to 11 level 1 trauma centers in the state; 22% (95% CI: 19.9%-24.3%) suffered new pupillary asymmetry at any point during admission, 18% (95% CI: 12.6%-25.0%) suffered new motor deficit, and 22.4% (95% CI: 20.2-24.8) experienced death at 2 weeks.

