#### Data Safety and Monitoring Board

A DSMB of 4 experienced trauma neurosurgeons and neurointensivists of international standing will be constituted, who will review every suspected unexpected critical neuroworsening event, as defined above, in each arm of the study. All critical neuroworsening events will be reported to the medical monitor (a neurosurgeon) within 24 hours, who will review expectedness, and refer all unexpected serious adverse events (SAEs) to the DSMB. If an unexpected SAE is suspected, ongoing ELD CSF drainage will be paused. The DSMB will review all intervention-related critical neuroworsening events and present a decision to the steering committee within 48 hours. A minimum of 3 DSMB members will independently review SAE. If the DSMB concludes that a critical neuroworsening event was not related to intervention, participant may continue study procedures per protocol. If, however, DSMB deems a neuroworsening event to be related to intervention, and if a discrete contributing factor is identified, the steering committee will meet within 7 days to review the report and discuss necessary changes to protocol before further enrollment.

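### The board that adjudicates the primary safety count also judges relatedness to the drain, and the article describes no masked decision on whether an event occurred

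*Protocol article*

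**What the plan says.** - **Design.** The Study Design section describes a "multisite randomized, allocation-concealed, open-label, safety and feasibility clinical trial". Concealment applies to allocation only.
- **Primary safety outcome.** Under Outcomes, Primary Outcomes, it is the "Frequency of critical neuroworsening adverse events between the intervention and treatment arms as adjudicated by Data and Safety Monitoring Board".
- **What the board decides on a case.** The section on the Data Safety and Monitoring Board (DSMB) describes a relatedness judgement with two results. One is "If the DSMB concludes that a critical neuroworsening event was not related to intervention, participant may continue study procedures per protocol". The other applies if the "DSMB deems a neuroworsening event to be related to intervention, and if a discrete contributing factor is identified", and it sends the matter to the steering committee before further enrolment. The timetable reads: "The DSMB will review all intervention-related critical neuroworsening events and present a decision to the steering committee within 48 hours". At least three members review each serious adverse event independently.
- **What reaches the board.** The same section gives its scope as events "who will review every suspected unexpected critical neuroworsening event, as defined above, in each arm of the study". The medical monitor stands in front of it, "who will review expectedness, and refer all unexpected serious adverse events (SAEs) to the DSMB".
- **What counts as an event.** Item 1 of Table 2 (Risks to Human Subjects) is a "Spontaneous decrease in the GCS motor score of ≥1 points (compared to previous exam". Items 2 and 4, a new fall in pupillary activity and a new focal motor deficit, carry no numeric threshold.

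**The concern.** Whether a drain caused an event can be asked only by someone who knows there was a drain. The board that asks this also supplies the count on which the arms are compared. If it knows the arm when it settles an ambiguous case, that knowledge can enter the count.

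Ambiguous cases are likely in this population. Tiers 1 and 2 of Table 1 allow more sedation and analgesia, and neuromuscular paralysis. A one-point motor fall may therefore be spontaneous or may follow a drug. Knowing that CSF is being drained, a reviewer may be readier to call the fall an event. A reviewer may equally be readier to put it down to sedation.

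The expected result is no increase in events with ELD, and the section on expected outcomes makes that the condition for designing a phase 2/3 trial. A small shift in the count therefore bears on the main decision the trial is meant to inform.

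**Working it through.** The article states no error rate, margin or calculation behind the sample size, so there is no figure of its own to reproduce. The check is a reading of the text followed by simple arithmetic.

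**Step 1: the roles side by side**

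| Question | Who answers it | Is the arm needed? |
|---|---|---|
| Did a Table 2 event occur? (primary count) | DSMB, per Primary Outcomes | No |
| Was it related to the intervention? | DSMB, per the DSMB section | Yes |

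The first question can be answered without the arm and the second cannot. The article gives both to one board and describes neither an order between them nor masking for the first.

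**Step 2: which items are exposed**

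- *Judgement needed:* item 1 (was the fall spontaneous?), item 2 (is the pupillary change a new decrease?) and item 4 (is the motor deficit new and focal?).
- *Less exposed:* pupil size and symmetry measured by automated pupillometry, and overt herniation.

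**Step 3: what one decision is worth**

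Input: 30 patients (Randomization section). The text gives no allocation ratio and the randomisation figure is not shown, so the group sizes below are assumptions. Incidence is taken as the proportion of patients with at least one event, and the reclassified patient is assumed to have no other event that counts.

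Shift in a group's incidence = 1/n.

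- n=10 (one of three equal arms): 1/10 = 10 percentage points
- n=15 (half the trial): 1/15 = 6.7 points
- n=20 (two ELD groups of 10 combined): 1/20 = 5 points

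If one patient is moved up in one group and one down in the other, the spurious difference is the sum of the two shifts:

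- 10 v 10: 10 + 10 = 20 points
- 15 v 15: 2/15 = 13.3 points
- 20 v 10: 5 + 10 = 15 points

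**Step 4: effect on a risk ratio**

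Suppose a fraction f of ELD events is discounted and no control events are. Then observed risk ratio = (1 − f) × true risk ratio. With a true ratio of 1:

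- f = 0.10 gives 0.90
- f = 0.25 gives 0.75
- f = 0.50 gives 0.50

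The values of f are assumed. If ELD events were over-called instead, the ratio would move above 1.

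**The case against.** **The article does not say that occurrence is judged unmasked.** This is the strongest reply, and it is right. The DSMB section can be read as safety oversight and the Primary Outcomes section as endpoint adjudication, and nothing says they are one procedure. The board is also said to review events in each arm. Relatedness to a drain is an empty question in usual treatment, so its review is unlikely to be about relatedness alone. A full protocol or charter could contain a masked first step. A reader might infer that a single unmasked review settles both questions, but the text does not support that. What stands is narrower: the article gives both tasks to one board, one of them needs the arm, and no separation is described.

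**Adjudication is not the only point of entry.** Detection at the bedside is open-label, and the monitor's expectedness decision comes before the DSMB. A reader might infer that masking the adjudicators would make the primary outcome unbiased. It would not. It protects only the classification of cases that reach the board.

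**The 22% background rate does not measure the problem.** A reader might multiply it by 10 patients to get 2.2 ambiguous events per arm. That rate is for new pupillary asymmetry, which is item 3 of Table 2 and not one of the items that turn on judgement. The documents give no rate for ambiguous events.

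**Sampling error is larger than one reclassification.** With 22% used only as a convenient proportion and 10 patients per arm, the standard error of a difference is √(2 × 0.22 × 0.78 / 10) = 0.185, or 18.5 points. That is correct and limits the weight of this point. Wide sampling error does not correct a systematic shift, however, and this one can be reduced cheaply.

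**Masking will be imperfect.** After ELD placement, checks run every 15 minutes for an hour; otherwise they are hourly. Raw serial data from that hour would show the arm. The packet has to be designed around this.

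**Conclusion.** The point holds as a design weakness that is cheap to reduce. It is not a demonstrated bias. In an open-label trial, the board that supplies the adjudicated primary safety count also judges relatedness, and no masked decision on occurrence is described. Judgement-dependent Table 2 items could therefore be classified differently by arm.

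Each reclassified patient is worth 10, 6.7 or 5 percentage points at 10, 15 or 20 patients in the group. This rests on assumed group sizes and on counting patients with at least one event. The number of patients at risk of reclassification is unknown, as is the direction. A reader might infer that the arrangement favours ELD because no difference is expected; over-calling events when a drain is present is just as possible.

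**What to change.** Amend Primary Outcomes and the DSMB section to split the board's work into two recorded steps for every suspected event put to it for the primary outcome, in any arm.

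1. **Occurrence, masked.** The same minimum of three members record whether a Table 2 event occurred. They use a uniform packet without arm, drain output or drain notes. It shows a fixed number of examinations before and after the event without clock intervals, so that the 15-minute checks do not reveal the arm. It also gives the timing of sedatives and paralytics relative to the event, and cranial CT. This recorded vote is the primary outcome.
2. **Relatedness, unmasked.** The arm is then disclosed and relatedness is judged for the steering committee.

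The rule on pausing drainage and the 48-hour decision stay as written and do not wait for the masked vote.

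**Cost.** Coordinator time for redaction and one extra form. The reviewers are the same. Table 4 already covers GCS, pupil and pupillary index data, ICP, medications and cranial CT. Some unmasking will remain. Because sites are already enrolling, the change should be made soon, and any event classified before it should be identified in the report.

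This does not address which events are referred to the board. The article words that scope in more than one way, and it needs to be reconciled separately.

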### Adverse Events Reporting

#### Local Institutional and Central IRB

All critical neuroworsening events in intervention arms will be reported to the medical monitor who will make determination of expectedness, and if deemed unexpected will be further reported to local site institutional IRB, central IRB, and DSMB within 24 hours.

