## DATA MANAGEMENT AND STATISTICAL ANALYSIS

All data including screening, inclusion/exclusion criteria, e-consent, randomization, and clinical data from all patients will be collected directly into a centralized electronic case report form supported by the MTBI^2^ Collection, Access, Sharing, and Analytics (CASA) platform system based in Henry Jackson Foundation Bethesda. National Institute of Neurological Disease and Stroke TBI-related common data elements from the following domains will be used: patient characteristics and history, disease/injury-related events, assessments and examinations, treatment/intervention data, protocol experience, and outcomes and end points (32) (Table 4).

**TABLE 4. T4:** Common Data Elements Collected: Domains, Measures, and Instruments

Domain	Subdomain	Measures/instruments
Participant characteristics and history	Demographics	Age, race/ethnicity, sex/gender, socioeconomic status, military service
	General health history	Significant medical history
Disease/injury Related events	Classification	Baseline risk assessment
		Injury severity score
		Head AIS
	History of disease/injury event	Injury presentation^a^
		Type, place, cause and mechanism of injury
	Discharge information	Discharge destination, time, and vital status
	Second insults	Aspiration, cardiac arrest, hyperventilation, hypotensive episode, seizure
		EEG monitoring
Assessments and examinations	Physical/neurological examination	Glasgow coma scale
		Pupil size, shape, and reactivity
		neurological pupil index
	Vital signs and other body measurements	Height and weight
		ICP monitoring
	Imaging	Cranial CT data
	Laboratory tests	Laboratory results (including INR and platelet count)
Treatment/intervention data	Surgeries and other procedures	ER/admission therapeutic procedures
		Surgical and therapeutic procedures
		Intraoperative management
	Therapies	Therapy intensity level
	Drugs	Prior and concomitant medications
Protocol experience	Participant/subject identification, eligibility, and enrollment	Informed consent
	Off treatment/off study	Study discontinuation/completion
Outcomes and end points	Disability	Glasgow outcome scale
	Adverse events	Severity: common terminology criteria for adverse events v6.0
		Expectedness: NIA adverse event and serious adverse event guidelines
		Causality: NIA adverse event and serious adverse event guidelines
		Neuroworsening events

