## OUTCOMES

### Primary Outcomes

Both “intention-to-treat” and “treated as per protocol” analyses will be performed. Incidence of critical neuroworsening events will be compared between each arm, and between both ELD groups and control arm. Univariate and multivariable analyses will be performed using baseline variables, hourly NPI change, and volume of CSF drained per day for outcomes, ie frequency of neuroworsening events and death. Multivariable analyses will use stated adverse outcomes as dependent variables, and age group, sex, baseline ELD safety score, and pupillary abnormality as independent variables. Logistic regression will be performed using those variables that have an association with outcome with a *P*-value of ≤.10.

For feasibility, a comparison between proportion of patients in each arm who underwent ELD as per protocol will be performed. Comparison between the 2 ELD groups will be performed. Interactions will be tested for in all analyses.

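### The primary safety outcome counts DSMB-adjudicated events, but the referral rules send the DSMB only unexpected events and disagree on which arms are covered, leaving two different primary numerators

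*Protocol article*

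**What the plan says.** The outcome definition (Primary Outcomes under Methodology) is "Frequency of critical neuroworsening adverse events between the intervention and treatment arms as adjudicated by Data and Safety Monitoring Board (DSMB". The events are those in Table 2, and the definition sets no limit by expectedness or relatedness.

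The adverse event sections then describe how events reach the board:

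- Local Institutional and Central IRB: "All critical neuroworsening events in intervention arms will be reported to the medical monitor who will make determination of expectedness". Of these, only the ones that the monitor judges unexpected go on to the IRBs and the board.
- Data Safety and Monitoring Board, scope of the board: "who will review every suspected unexpected critical neuroworsening event, as defined above, in each arm of the study".
- Same section, role of the medical monitor: every critical neuroworsening event goes to the monitor within 24 hours, with no restriction by arm. The monitor is the person "who will review expectedness, and refer all unexpected serious adverse events (SAEs) to the DSMB".
- Same section, further on: "The DSMB will review all intervention-related critical neuroworsening events and present a decision to the steering committee within 48 hours".

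The analysis section (Primary Outcomes under the later Outcomes heading) says "Incidence of critical neuroworsening events will be compared between each arm, and between both ELD groups and control arm". It mentions neither adjudication nor expectedness. Data Management and Statistical Analysis says that "clinical data from all patients will be collected directly into a centralized electronic case report form", and Table 4 lists neuroworsening events among the outcomes.

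**The concern.** Expectedness is a regulatory classification. It decides how quickly an event must be reported and to whom. It does not say whether an endpoint event occurred. Here it stands between the event and the body whose adjudication defines the primary outcome.

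The filter could bite. In Risks to Human Subjects, the article's own database analysis gives 22% with new pupillary asymmetry and 18% with new motor deficit. Both are Table 2 events. A monitor could plausibly regard many such events as the expected course of severe TBI, or as known risks of drainage, since the same section describes them that way.

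The trial is open-label and no masking of the monitor is stated. According to Expected Outcomes of the Study, a phase 2/3 trial follows if ELD does not increase serious adverse events. A numerator shaped by referral could hide a harm or create one, and either could affect that decision.

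**Working it through.** The plan gives no figure to reproduce on this point. The check compares the passages first and then illustrates the size.

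**Step 1. The routes side by side**

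| Place in the article | Arms covered | Filter before the DSMB or the analysis |
|---|---|---|
| Outcome definition | All | None stated; DSMB adjudicates |
| Local Institutional and Central IRB | Intervention arms | Unexpected only |
| DSMB section, scope of the board | Each arm | Suspected unexpected only |
| DSMB section, monitor's referral | All events to the monitor | Unexpected serious adverse events only |
| DSMB section, later sentence | Not stated | Intervention-related |
| Analysis section | All | None; adjudication not mentioned |

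No row brings expected control-arm events to the board. The intervention-related row is also circular: the same section has the DSMB decide relatedness, and a control patient without a lumbar drain can hardly have an event related to one.

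**Step 2. Inputs for the illustration**

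- Risk p = 0.22, with 0.18 as a check (Risks to Human Subjects). The same p is used in every arm, so there is no true ELD effect. Each figure covers only one of the five Table 2 event types. The 22% counts events at any point in the admission, whereas the trial measures outcomes other than mortality during intensive care only.
- 30 patients (Randomization). The text gives no allocation ratio and the figure is not shown. Assumed: 20 ELD and 10 control, with 15 and 15 as a check.
- Share of events called unexpected, u = 1, 0.5 or 0.2. These values are assumptions.

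**Step 3. Each-arm rule, same u in all arms**

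Expected number reaching the board = n × p × u.

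- True counts: 20 × 0.22 = 4.4 ELD and 10 × 0.22 = 2.2 control.
- u = 0.5: 2.2 and 1.1 are seen, so 50% are never adjudicated.
- u = 0.2: 0.88 and 0.44 are seen, so 80% are never adjudicated.
- Chance that the board sees no event in 30 patients at u = 0.2: (1 − 0.22 × 0.2)^30 = 0.956^30 ≈ 0.26. At u = 0.5: 0.89^30 ≈ 0.03.

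The share lost is 1 − u, whatever p and the allocation are.

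**Step 4. Intervention-arms rule**

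The control count is 0 by construction, so the spurious risk difference is p × u − 0.

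| p | u = 1 | u = 0.5 | u = 0.2 |
|---|---|---|---|
| 0.22 | +0.22 | +0.11 | +0.044 |
| 0.18 | +0.18 | +0.09 | +0.036 |

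These differences do not depend on the allocation.

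**Step 5. All arms referred, but expectedness judged differently**

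Apparent risk ratio = u(ELD) / u(control), and risk difference = p × (u(ELD) − u(control)).

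- 0.2 in ELD and 0.5 in control: ratio 0.4, difference 0.22 × (−0.3) = −0.066.
- 0.5 in ELD and 0.2 in control: ratio 2.5, difference +0.066.

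The true ratio is 1 in both cases, so the bias can run either way.

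**Step 6. All events adjudicated**

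Expected counts are 4.4 and 2.2 with a 20:10 split, or 3.3 and 3.3 with 15:15. The risk difference is 0 in both, as it should be with no true effect.

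**The case against.** The referral text stands under Safety Considerations, and its first part is headed for the IRBs. It can fairly be read as the expedited-reporting path and not as endpoint ascertainment. All patients have hourly neurological monitoring, all data enter the electronic case report form, and the analysis section compares incidence in all arms without a filter. This is also a condensed article, and adjudication procedure is often left to a charter.

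Much of this stands. It shows that the data need not be lost and that an unfiltered comparison is possible. It does not remove the conflict: the outcome is defined by DSMB adjudication, the only described ways to the DSMB are filtered, and the unfiltered analysis does not mention adjudication. These are explicit statements that disagree, so the point does not rest on missing detail.

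Three stronger readings are tempting, and the documents do not support them.

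- **Control events never reach the board, so the comparison is necessarily biased by arm.** This follows only if the IRB paragraph or the intervention-related sentence is read alone. The DSMB section sends all events to the monitor and speaks of each arm.
- **Most events would be screened out.** The background rates make some filtering plausible, but Table 4 refers expectedness to NIA guidelines that are not shown. No passage says that background TBI events will be classed as expected.
- **The risk is 40%, from adding 22% and 18%.** One patient can have both events, so 40% is only an upper bound for these two types together.

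**Conclusion.** The concern holds as a conflict over the primary safety numerator. The article supports two counts, events adjudicated by the DSMB after a filter and all recorded events, and does not say how they fit together.

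If the adjudicated count is used, either referral rule leaves it incomplete whenever any event is called expected. Bias by arm is conditional. It arises if the intervention-arms or intervention-related scope applies, or if expectedness is judged differently between arms, and its direction is not fixed.

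The sizes in the working are illustrations. They rest on equal risk in all arms, single-component background rates, and assumed shares called unexpected. The expected counts by arm also rest on the assumed allocation. They show that the effect could be large relative to the few events expected in 30 patients; they do not predict what will happen.

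The matter should be settled before the data lock is lifted. Choosing between the two counts after that would be post hoc, in a trial whose main purpose is safety.

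**What to change.** Reconcile the outcome definition, the two adverse event reporting sections and the analysis section:

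1. State that every Table 2 event in every arm, whatever its expectedness or relatedness, goes to endpoint adjudication in the same form, with arm masked where feasible.
2. State that the primary safety outcome counts all events confirmed by that adjudication, and say so again in the analysis section.
3. Limit expectedness and relatedness to expedited safety reporting.
4. Give one description of which arms and which events the DSMB reviews for each purpose.

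Masking is a desirable addition; the conflict can be resolved without it. Adjudicating relatedness alone would not be a substitute, because it has no clear meaning for control patients and cannot be judged with the arm masked.

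The cost is a wording amendment and some additional event packets for the existing DSMB, in a trial of 30 patients.
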